	**%/Mean, SD (range)**
Gender	
% male	55
Age	57.1, 7.1 (44.9–70.9)
Native country	
% the Netherlands	95
Education level*	
% low	54
% intermediate	23
% high	23
Hypertension	
% Hypertensive	52
Body Mass Index	27.4, 4.6 (15.2–46.7)
% < 18.5	1
% 18.5–25	31
% 25–30	45
% >= 30	22
Smoking behavior	
% nonsmokers	78
Alcohol consumption**	
Glasses/day	1.1, 1.4 (0–9)
% meeting guideline	86
Saturated fat intake	
Fat score	17.8, 5.9 (2–37)
% meeting guideline	30
PA	
Hours/week moderately physically active	4.7, 3.8 (0–20.2)
% >= 2.5 hours/week moderately physically active	61
Days/week moderately physically active	2.2, 1.6 (0–7)
% >= 5 days/week moderately physically active	6
% meeting guideline combined	0
Fruit consumption	
Pieces of fruit/day	2.1, 1.6 (0–8.9)
% >= 2 pieces/day	41
Days/week at least 2 pieces/day	3, 2.5 (0–7)
% >= 7 days/week at least 2 pieces/day	13
% meeting guideline combined	11
Vegetable consumption	
Grams of vegetables/day	165.2, 82.4 (0–494.7)
% >= 200 grams/day	31
Days/week at least 200 grams/day	4.1, 2.0 (0–7)
% >= 7 days/week at least 200 grams/day	11
% meeting guideline combined	7

* Education level was classified as: low in participants with no education, primary, lower secondary vocational, preparatory vocational or junior general secondary education; intermediate in participants with senior secondary vocational, technical secondary, upper vocational secondary, senior general secondary or university preparatory education; and high in participants with higher professional or university education [125-127].

** Participants were classified as meeting the alcohol consumption guideline if they consumed fewer than 3 glasses a day (men) or fewer than 2 glasses a day (women) [10].

Participants were stratified and randomized into the following four groups by a computer program.

1. The tailored print communication (TPC) group, in which participants received four tailored letters. The first and third letter focused on PA, the second and fourth on fruit and vegetable consumption, and the fourth also addressed fat intake.

2. The telephone motivational interviewing (TMI) group, in which participants received four telephone calls based on MI. Participants chose the order of the conversation topics in the first and third call. If they chose to focus on PA in the first call, fruit and vegetable consumption was discussed in the second, and vice versa; they could also choose to discuss fat intake in the fourth call.

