#### Hypotheses

Effect size estimates for our intervention and control conditions were difficult to determine, because similar studies were not available at the start of Vitalum (2003). However, one study on MI [48] and others on computer tailoring [27,33,40] found increases of at least 10% in one or more of the target behaviors (i.e., PA, fruit or vegetable consumption, or saturated fat intake) in participants who received single or multiple MI or tailoring compared to control group participants. As PA and fruit and vegetable consumption will receive more attention than saturated fat intake, we also expect to find larger effects for these. Therefore, we formulated the following hypotheses:

1. Compared to those in the control group, participants receiving either TMI or TPC will (a) increase PA as well as fruit and vegetable intake by 10% at the first follow-up from the expected mean at baseline; and (b) decrease saturated fat intake by 5%.

2. Participants receiving TPC+TMI will have resulting behavioral changes which exceed the sum of the changes expected given each intervention.

3. Participants with a low education level benefit more from TMI than TPC.

4. Participants without hypertension benefit more from TMI than TPC.

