### Statistical analyses

#### Sample size and power

The required sample size was determined using the formula for unpaired *t*-tests [114], as each effect test in a balanced 2 × 2 between-subject design (i.e., the TMI and the TPC main effects and their interaction) comes down to such *t*-tests (apart from having less residual variance). The sample size calculation was based on the following assumptions: (a) since results of similar studies were not available at the start of Vitalum, the sample size calculation was based on a small expected effect size (Cohen's d) of .3 [115]; (b) a power of .9; (c) an alpha of .01 to correct for multiple testing; (d) an intra class correlation of .02, where the correlation is based on random treatment by GP interaction (a random GP main effect does not affect the sample size in the event of person randomizations within GPs) [116]; and (e) an expected average number of participants per general practice of 70. Loss of power due to random dropout or a gain in power from including the pretest as a covariate in the analyses [117] was not taken into account in the sample size calculation. However, the loss of power due to 20% random dropout can be compensated by including the pretest as a covariate if it correlates .5 with the posttest – the latter correlation being a realistic assumption. These assumptions resulted in a required sample size at baseline of 1,600. Thus, Vitalum aims to assess 400 participants per group at baseline. Assuming 50% of people refuse participation, and 40% of the remaining group meet the recommendations for PA and nutrition and are thus excluded, at least 5,400 people must be invited to secure 1,600 for the study.

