#### Cost-effectiveness analysis

A cost-effectiveness analysis of Vitalum will be executed if the interventions are found to affect the primary outcome measures [118]. The cost-effectiveness analysis, executed from a healthcare viewpoint, examines the costs and effects of intervention implementation. Direct medical costs involved in carrying out the intervention (e.g., printing and mailing letters for TPC, call charges for TMI) are measured [118]. Other healthcare consumption costs are expected to be equal between the groups and are therefore not part of the analysis. Because Vitalum's goal was to examine the intervention's effectiveness, the developmental costs of the intervention are considered sunk costs and not included in the cost-effectiveness analysis. This also holds for protocol-driven costs (i.e., costs of data gathered as part of a clinical trial [118]); for example, the cost of recording the motivational interviews or that associated with measuring control group participants' behavior and its determinants. Direct non-medical costs (e.g., traveling costs, which were not applicable to Vitalum) and indirect non-medical costs (e.g., productivity costs) are irrelevant given the healthcare perspective chosen.

Since Vitalum may affect both health behavior and health-related quality of life, cost-effectiveness analyses will focus on both levels. To measure cost-effectiveness on a behavioral level, Vitalum's primary outcome measures will be combined into two overall outcome measures: the percentage of improvement in a participant's health behaviors compared to baseline measured using multiple-item measurements; and the number of public health guidelines met by a participant according to the combined measure (0–3: PA, fruit consumption and vegetable consumption). Intervention costs per patient who improved at least 10% of one health behavior as well as costs per patient who reached a specific number of public health guidelines will be examined. For health-related quality of life, the average improvement in quality of life score (Quality Adjusted Life Years) will be assessed by the RAND 36-item Health Survey 1.0 [101,102], and intervention costs per patient related to health-related quality of life score will be examined.

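### The planned cost per patient improving at least 10% counts people who would have improved without any intervention effect and names no incremental ratio against control, and a RAND-36 score change is labelled QALYs.

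*Protocol article*

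**What the plan says.** All of this stands in the protocol article, section Cost-effectiveness analysis, unless another place is named.

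- The first behavioural measure is "the percentage of improvement in a participant's health behaviors compared to baseline measured using multiple-item measurements". The second is the number of guidelines met ("0–3: PA, fruit consumption and vegetable consumption") on the combined measure.
- The quantities to be reported are "Intervention costs per patient who improved at least 10% of one health behavior as well as costs per patient who reached a specific number" of guidelines.
- Costs are those of delivering the intervention. Other healthcare costs are left out because they are expected not to differ between groups.
- The analysis is run only if the interventions turn out to affect the primary outcomes.
- For quality of life, "the average improvement in quality of life score (Quality Adjusted Life Years) will be assessed by the RAND 36-item Health Survey 1.0".
- Table 1 gives a minimum of 0 for moderate activity hours, fruit and vegetables.

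**The concern.** The denominator of the first ratio is a count of people whose self-reported behaviour rose by a tenth from their own starting value. Self-reports of activity and diet vary widely between two occasions, and each person has up to three chances to qualify. Many will therefore qualify through ordinary variation. If the control group's share is not subtracted, these people are counted as benefit bought by the intervention.

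Two things are then at stake. The cost per success looks far lower than the cost of each success the intervention adds. And because the responder share is already high without any effect, the ratio mainly ranks the arms by delivery cost, while the Background gives comparing the cost-effectiveness of the two methods as an aim.

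The quality-of-life label is a separate matter. A QALY is a preference-based utility multiplied by time. The Secondary outcome measures section describes the RAND-36 as a set of health domains, and a mean change in such scores is a different quantity.

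**Working it through.** **Inputs from the article**
- Baseline mean, SD (range), Table 1: activity 4.7, 3.8 (0–20.2) hours/week; fruit 2.1, 1.6 (0–8.9) pieces/day; vegetables 165.2, 82.4 (0–494.7) g/day.
- Pre-post correlation r = .5, from Sample size and power: dropout loss "can be compensated by including the pretest as a covariate if it correlates .5 with the posttest".
- Hypothesised effect, from Hypotheses: "increase PA as well as fruit and vegetable intake by 10% at the first follow-up from the expected mean at baseline".
- Effect used for power: d = .3.

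**Assumptions, not in the article**
- Margins: gamma, log-normal, or normal clipped to the observed range.
- r varied from .5 to .9.
- Correlation between behaviours from 0 to .4.
- No change in mean or SD without intervention. Regression to the mean after selecting people below the guidelines is not modelled and would probably raise the rates.

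**The plan's own figure.** The article gives no responder rate to reproduce. Its sample size does reproduce: n = 2(2.576 + 1.282)²/.3² ≈ 331 per side, 662 in total. Multiplied by 1 + 69 × .02 = 2.38, this gives 1,576, close to the stated 1,600. So d = .3 is the effect the trial is sized for. A 10% gain is smaller: .47/3.8 = .12, .21/1.6 = .13 and 16.52/82.4 = .20 SD.

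**Step 1: responders with no effect.** A responder has follow-up of at least 1.10 × baseline on at least one of three behaviours. Ranges are over the three margins.

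| Pre-post r | Between-behaviour 0 | .2 | .4 |
|---|---|---|---|
| .5 | 82–83% | 77–78% | 71–73% |
| .7 | 79–82% | 74–76% | 69–71% |
| .9 | 72–76% | 67–71% | 62–66% |

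If 'one health behavior' means one named behaviour, the share is about 42–46% at r = .5 and about 32–46% over all settings.

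**Step 2: how little the ratio can move.** Let C be the delivery cost per person and p the responder share. Cost per responder is C/p. With no effect it is C/.83 = 1.2C to C/.62 = 1.6C. With a perfect intervention it is 1.0C. An arm costing more than 1.2 to 1.6 times another could not look better on this ratio, even if it worked in everyone and the cheaper arm in no one.

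**Step 3: cost per additional responder.** This is C/(p1 − p0), where p1 is the share with the effect and p0 the share without. It exceeds cost per responder by the factor p1/(p1 − p0).
- Gamma, r = .5, independent behaviours, 10% of the baseline mean added to each behaviour: p0 = .830, p1 = .8905. Cost per responder is 1.12C, cost per additional responder 1/.0605 = 16.5C, factor about 15.
- Same setting, d = .3 on each behaviour: p1 = .932. The figures are 1.07C and 1/.102 = 9.8C, factor about 9.
- Log-normal, r = .9, between-behaviour .4, 10% of the mean added: p0 = .621, p1 = .827. The figures are 1.21C and 1/.206 = 4.9C, factor about 4.
- Over the grid: about 4–15 for 10% of the mean added, about 5–19 if the gain is a 10% multiple of each person's value, and about 3–9 for d = .3.

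**Step 4: zero baselines.** The individual measure is (follow-up − baseline)/baseline. At baseline 0 it does not exist, and just above 0 a trivial rise passes 10%. Table 1 shows that zeros occur on all three behaviours, but not how many.

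**Step 5: the QALY label.** The section equates an average score improvement with QALYs. It names neither a utility weighting of the RAND-36 items nor a weighting by time.

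**The case against.** - **A comparison with control may be intended.** Leaving out other healthcare costs because they should be equal across groups, and excluding the cost of measuring controls, makes sense only if arms are compared. A condensed article may leave the form of the ratio to the full plan. This stands in part: a reader might infer that the article excludes a comparison with control, and it does not. But the ratio it spells out is a within-arm one.
- **The analysis is conditional.** A reader might infer that a wholly ineffective programme would be presented as good value. The condition prevents that, because no cost analysis follows if nothing works. It does not protect against crediting a weak arm alongside an effective one, and it leaves the no-effect improvers in every arm's count.
- **The rates are simulated.** This stands. A single figure such as 80%, or a single factor such as 19, would claim more than the article supports. The top factor needs gamma margins, r = .5, independent behaviours and a multiplicative gain.
- **Guidelines met is already planned as a second behavioural outcome.** This stands. Its baseline shares are low (activity 0%, fruit 11%, vegetables 7% on the combined measure), and no comparable inflation is shown for it.
- **The QALY parenthesis may abbreviate a conversion.** RAND-36 items are collected at baseline and both follow-ups, so one could be derived. As printed, however, the score improvement itself is called a QALY.
- **Policy use of the cost figures.** A reader might infer that this is a stated aim. The Discussion ties policymakers to the efficacy results and says cost-effectiveness is not the primary goal.

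**Conclusion.** The concern holds for the ratio as named and for the QALY label. With no intervention effect, roughly 62–83% of participants would count as improved on at least one of three behaviours (about 71–83% at the article's r = .5), or about 32–46% on one named behaviour. Cost per additional responder would exceed cost per responder about 4–19 times for a 10% gain and about 3–9 times for d = .3. These ranges rest on the Table 1 means and SDs, assumed margins, and a between-behaviour correlation the article does not give. The direction does not depend on these choices: in every setting most people qualify on at least one behaviour without any effect. The missing rule for zero baselines is a smaller defect of the same measure. The label error needs no calculation. All of this touches a conditional secondary analysis only.

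**What to change.** - State that cost-effectiveness is incremental: difference in mean cost and difference in effect, each arm against control and arm against arm, with bootstrap intervals.
- Take as behavioural effects the already planned number of guidelines met and the baseline-adjusted absolute change in each behaviour. Drop the individual 10% responder, which also removes the zero-baseline problem.
- For quality of life, either derive a preference-based utility from the RAND-36 items and take the baseline-adjusted area under the curve over the measured time points, or call the outcome RAND-36 score and drop the QALY label. If the area is used, settle the first follow-up time: the Secondary outcome measures section gives week 43, other sections week 47.

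The cost is some rewording and recoding of data already collected. The reported cost per success will look less favourable.

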## Discussion

This paper described the design of the Vitalum study. Vitalum aims to evaluate the efficacy of TMI and TPC in changing PA and fruit, vegetable and fat intake among Dutch adults aged 45 to 70. Its strengths are: (a) testing TPC and TMI for multiple behaviors; (b) evaluating TPC versus TMI and both versus TPC+TMI; (c) testing TPC and TMI for people with expected different motivational stages (e.g., participants with and without hypertension); and (d) testing TPC and TMI for people with different education levels.

Vitalum's development was accompanied by practical and operational difficulties. First, although the recruitment of participants via GPs resulted in the required number of participants, this method was time consuming and difficult for both researchers and GPs. GPs had to invest time by providing participant data and excluding certain people; yet, since GPs prioritize patient care and cure and not research, recruitment took more time than planned. Second, the data had to be collected and treated in batches. Combined with the recruitment delay this meant that 18 months lapsed between the enrollment and baseline data collection of the first and last groups. Third, questionnaires with many items were needed to measure and target multiple behaviors and their determinants [25]. This may have increased chances of dropout and invalid data due to participants becoming annoyed [119]. Furthermore, although telephone surveys were planned to reduce dropout risk, they appeared too restrictive and more expensive than paper questionnaires. Thus, paper questionnaires were used to collect baseline and posttest data. To reduce dropout risk, however, we used telephone surveys (at 25 and 39 weeks after baseline) instead of paper questionnaires to gather new data for the computer tailoring interventions. Moreover, although sometimes recommended, we could not use relatively objective reference instruments such as biomarkers for fruit and vegetable consumption [99,120] to validate the self-report questionnaires because they were considered too time consuming and expensive [67,95]. We thus used validated self-report questionnaires only [97,99,100]. Also, participants were more likely to suffer from hypertension than non-participants. This may be caused by selection bias, in that people with hypertension are more willing to participate than those without. This was confirmed by the fact that people who completed the baseline questionnaire were also more likely to suffer from hypertension than people who were excluded or refused to participate. However, this bias may also have been increased by including participants who failed to meet at least two guidelines, since high blood pressure is associated with lack of physical activity and low fruit and vegetable consumption [8]. In addition, the cost-effectiveness analysis does not meet the criteria of a full economic evaluation from a societal perspective; but the cost-effectiveness outcome is not the primary goal of our study. Finally, participants in the TPC group received stage-matched advice based on the stages of change algorithm of the Transtheoretical Model [72]. Although the usefulness and validity of stage models in nutrition and PA research has been criticized [105,121,122], their use in tailoring is still regarded promising [123].

Despite these difficulties, Vitalum aims to generate data on the efficacy of TPC and TMI in changing health behaviors. Its results will help policymakers decide which approach deserves future dissemination; the results on nutrition behavior and PA may also be of value in preventing other risk factors and diseases such as cancer or diabetes [1,7,8,124]. Vitalum's results are expected in July 2008.

## Appendix

### Example of stage-matched tailored PA advice to a contemplator

#### What are your future plans?

The next part of the letter concerns the future. What plans do you have with regard to physical activity? Do you want to increase or maintain your activity level?

You mentioned in the questionnaire that you have plans *to increase your physical activity level to 5 days a week for 30 minutes a day*. You also indicated that you want *to execute this plan within the next 6 months*. This means that you seriously plan to change your activity level. The following information about the advantages of being more physically active may help you in your preparation.

You indicated in the questionnaire seven reasons why increasing your physical activity level would benefit you; that if you are physically active 5 days a week for 30 minutes a day:

- *you will consider yourself a better person;*

- *you will consider yourself a 'sporty' person;*

- *you will be proud of yourself;*

- *you will feel younger;*

- *you may lose weight;*

- *you will decrease your chances of cardiovascular diseases;*

- *you will meet new people*.

There are good reasons why increasing your level of physical activity is important: your health as well as your physical condition will improve. After 30 years, your muscle and bone strength declines. This is a natural process, but is substantially delayed by being physically active. This means you will be less likely experience bone fractures and will stay lithe.

Other advantages: being physically active positively affects your metabolism and bowel movement, and your risk for cardiovascular diseases and some types of cancer decreases. People who increase their level of physical activity consider themselves better people, are proud of themselves, and feel younger and sportier.

Finally, increasing your physical activity level is also good for your appearance and social contacts. Your chances of meeting people when out walking is higher than when watching a quiz show on television!

You also mentioned two disadvantages of increasing your physical activity level. You indicated that, if you are physically active on at least 5 days a week for 30 minutes a day:

- *You run the risk of an injury*. If you decide to increase your physical activity level, we recommend that you start easily. Take a break when you become tired – it is not a competition. It is also important that you wear good, solid shoes for walking.

- *You will sweat*. If you increase your physical activity level, your muscles produce more warmth. This warmth has to be lost to prevent your body temperature getting too high. Fortunately, you lose warmth by sweating; therefore, sweating is absolutely necessary to maintain a healthy body temperature. We recommend that you wear clothes with good ventilation when you exercise.

We hope that reading about the positive and possible negative sides of physical activity has reinforced your plans to increase your activity level in the next six months. We conclude this letter with advice that may help you achieve your goal.

First, it is important to choose the type of physical activity that suits you. We asked you in the questionnaire how you might increase your physical activity level. You indicated that:

- *You want to use your car less*. We often take the car without thinking, for example, to go shopping or to work, though these distances may also be easily walked or cycled.

- *You want to take a fast or brisk walk each day*. This is a very good idea. If you try to walk at a fixed time each day, this increases the chance that it will become a regular part of your day. By doing this, you can make physical activity a healthy habit.

- *You want to be more physically active in your spare time*. You may probably have some ideas about this. What one person likes, another might find boring or annoying. This also goes for physical activity. It is therefore important that you choose a type of activity that suits you; otherwise, the chance increases that it will not get past the planning stage, or that you will quit.
